**Figure 3. f3:**
[figure not shown]
Gantt chart of the assessment timeline in patients. Grey boxes are scheduled timepoints of respective assessments.

**
*Data management*
**

The multi-level data acquired from the enrolled participants would be quality-checked and de-identified to remove subject identifiers. These data would be stored with a coded identification. Different streams of data (ex. Clinical, MRI, EEG etc.,) would be linked using codes to facilitate seamless retrieval of different data types.

### Data analysis plan

Anonymized, coded data will be used for analysis. Pre-processing (where applicable – MRI/EEG data) will be done as per internationally accepted processing pipelines. Data analysis will be carried out in two phases – a) association and b) prediction. The first phase will involve exploratory analyses with biographic (age, sex, etc.) and disorder-specific (age-at-onset, medication, the severity of symptom, etc.) features that influence TMS-derived neuroplasticity metrics, MRI, EEG, HRV, and gene polymorphism measures. These include traditional bio-statistical procedures such as descriptive statistics and hypothesis testing for associations in order to identify any potential biomarkers of clinical response. Evaluation of clinical outcomes will be based on Last-observation carried forward analysis with secondary intent-to-treat analysis. The second phase of analysis will involve building predictive models that will be validated with an independent dataset. Here, instead of examining which individual measurements correlate with outcome measures, we seek to identify combination features (from resting-state fMRI as the primary objective; combining across data modalities will be the secondary objective) that can give the best prediction for the clinical outcome of proposed brain stimulation methods.

State-of-the-art feature engineering/machine learning methods such as gradient boosting/deep neural nets will be used to train the model on a part of the acquired dataset. Lastly, causal models using Bayesian networks or mediational analyses will be explored to uncover potential causal relationships between study variables.

**
*Data monitoring*
**

Formal committees

The data safety monitoring board, an independent advisory body, assesses data during the course of a study contributing to the scientific and ethical integrity of the study. It would periodically review and evaluate clinical efficacy and safety data collected during the study and assess reports on cumulated SAE. It consists of a biostatistician, psychiatrist, and ethicist specializing in psychiatry. Based on the DSMB charter, the board would provide a recommendation report on the continuation, modification, suspension, or termination of the trial to the study sponsor. The sponsor would submit the report to the ethics committees and trial management group (TMG) to decide on a further course of action.

TMG would comprise a group of investigators from the three collaborating institutes. It would monitor the day-to-day execution of the trial. It would take cognizance of trial participant drop-out in case of withdrawal of consent, non-compliance with study guidelines, and worsening of symptoms. It would interact with the DSMB and IEC. It would review the reports and recommendations of these oversight/monitoring committees and plan appropriate actions. It would decide on trial terminations and any trial modifications of the study procedures. It would also oversee the submission of modification, premature termination (if any), and final (completed) trial summary report to the IEC, trial registries, and funding agency.

The data management committee (DMC) comprises the principal investigators of the three institutes. It would be dedicated to reviewing the data archival, management, and sharing. It would execute the periodic data auditing and audit of the research practices related to the studies. It would ensure anonymization and de-identification of data. It would monitor the storage of data in the encrypted data storage servers. It would oversee the sharing of de-identified data upon reasonable requests from collaborators or the research community. Data sharing will be implemented as per the policy of DBT- Wellcome Trust India Alliance and International Good Research Practices in strict compliance with the ethics guidelines for biomedical research in India.

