Bagali *et al.*, 2023) and has been used as a sham protocol in previous TBS clinical trials (
Kohutova *et al.*, 2017). Since true TMS pulses will be delivered, the risk of participant bias will be minimal.

Two such sessions will be delivered each day, spaced across at least 3 hours for 15 days for a total of 30 sessions. The TBS and tDCS (active or sham) will be delivered one after the other in the same order for a given subject throughout the course of the intervention. The order of TBS and tDCS will be altered in consecutive subjects at each site.

Adherence to intervention

All sessions would be provided at the hospital by a team of researchers. The financial burden on the participants would be mitigated by covering the incidental expenses and reasonable compensation for their time and other costs. Adverse effects would be diligently monitored, and any discomfort to participants would be addressed. In case of intolerance to TBS, the highest tolerable dose below 120%RMT will be administered. The research subject will have easy access to the team of investigators to clarify any study-related queries. These measures would enhance intervention adherence and study retention.

Concomitant care

In case of any deviation from the study guidelines due to unforeseen situations, the same would be documented and reported. Participants with a change in antipsychotic dose of more than 25% from the dose at the initiation of the intervention or a change in the antipsychotic medication or other neuromodulatory interventions would be considered drop-outs. All ongoing psychotropic medications and psychosocial interventions would be allowed to be concomitant with the study intervention. No new interventions would be initiated during the study.

Outcome

The primary outcome measure would be a differential change in the resting-state functional brain connectivity after “cTBS+sham tDCS” vs “active tDCS+ im-TBS”. Functional MRI will be acquired at baseline and after the end of each step of the intervention. Identifying the resting state markers would partake seed-based connectivity approach around the stimulation-targeted as well as other hallucination related brain region including fronto-temporo-parietal opercular regions, insula, angular gyrus, hippocampus and parahippocampal gyri. (
Jardri *et al.*, 2011b;
Kühn & Gallinat, 2012;
Rollins *et al.*, 2019;
Thomas *et al.*, 2016;
van Lutterveld *et al.*, 2013;
Zmigrod *et al.*, 2016)

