Secondary outcome measures include broader clinical symptoms, adverse effects, and neurobiological parameters (The detailed protocol of neurobiological parameters will be described in a separate paper). Clinical symptoms would be measured by the auditory hallucinations rating scale (AHRS) (
Haddock *et al.*, 1999), Scale for assessment of positive symptoms (SAPS) and negative symptoms (SANS) (
Andreasen, 1983;
Andreasen, 1984), Calgary Depression Scale for Schizophrenia (CDSS) (
Addington *et al.*, 1994), Clinical Global Impressions (CGI) and Montreal Cognitive Assessment (MoCA) (
Nasreddine *et al.*, 2005) will be applied at baseline and every week till the end of the intervention. Cognitive and functional abilities will be assessed using the Brief Assessment of Cognition in Schizophrenia (BACS) (
Keefe *et al.*, 2004), Groningen Social Disability Schedule (GSDS) (
Wiersma *et al.*, 1988) and social and occupational functioning scale (SOFAS) (
Morosini *et al.*, 2000) at baseline and after each step of intervention.

Safety of the intervention sessions will be another secondary outcome measure: the tDCS-related adverse effect questionnaire Field (
Brunoni *et al.*, 2011;
Chhabra *et al.*, 2020) and the TMS-related adverse effects questionnaire Field (
Giustiniani *et al.*, 2022) will be used to monitor adverse effects after each intervention session.

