### Participant timeline

Step1: Patients meeting the selection criteria would be approached to participate in the study. A written informed consent would be obtained as approved by the ethics committees, after describing the study procedures with video aids. All treatments would be added to ongoing pharmacotherapy. In step-1, Participants would be randomised to either of the groups to receive “cTBS with sham-tDCS” or “active tDCS with sham TBS” twice a day for 15 days (over 3 weeks).

Step-2:

Upon non-response to step-1, participants would cross over to the other set of interventions in step-2 after a wash-out period of 2–4 weeks. Participants with <30% improvement in AHRS from baseline at the end of 2–4 weeks of the trial would be considered non-responders for inclusion to Step-2. Written informed consent would again be obtained before the initiation of step 2.

The order of TBS and tDCS would be maintained as was delivered in step-1 for the given participant (See
Figure 2).

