**Figure 2. f2:**
[figure not shown]
Depiction of the study procedure. In the first step of the study, the patients with persistent auditory verbal hallucinations would be randomized to receive 15 days of cTBS+sham-tDCS or sham TBS+active tDCS. Patients with clinical non-response even after 2–4 weeks of the end of the trial will be cross-covered to receive 15 days of the other set of interventions. Neuroimaging, and neurophysiological tests would be done before initiating and after the end of intervention with each step. Blood samples would be collected for genetic polymorphism assays at the baseline. Blue stars depict the time points of symptom rating and multimodal data acquisition. SZ: Schizophrenia, tDCS: transcranial direct current stimulation, cTBS: continuous theta burst stimulation, TMS: Transcranial Magnetic Stimulation, MRI: Magnetic resonance imaging, EEG: Electroencephalogram, TMS/tDCS: Transcranial magnetic stimulation/transcranial direct current stimulation, BDNF: Brain-derived neurotrophic factor, COMT: Catechol-O-methyltransferase.

**
*Sample size*
**

In order to identify a clinically relevant and appropriately corrected statistically significant signal from resting-state brain connectivity data with sufficient (~80%) power to differentiate (P<0.05) groups of responders and non-responders, a sample size ranging from 27 to 32 has been recommended for each group (
Pajula & Tohka, 2016;
Thirion *et al.*, 2007;
Zandbelt *et al.*, 2008) and similar sample size has shown utility in studies attempting to predict response (
Khalili-Mahani *et al.*, 2017;
Martens *et al.*, 2022;
Parlikar *et al.*, 2023;
Zhang *et al.*, 2022). Keeping with this, we will recruit 210 participants who will be randomized in part-1 of the treatment. Anticipating ~15% dropout, we will have ~180 participants who will complete the part-1 treatment. Assuming a third of the participants respond to either treatment arm, a sample of 60 and 120 will be categorised as responders and non-responders, respectively. We expect at least three-quarters of the non-responders to consent to the crossover treatment. Given our experience in a previous trial (

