Personality assessment	Mini International Personality Item Pool (Mini- IPIP)	Baseline
Depressive symptoms	Calgary Depression Rating Scale	Screening/Baseline, post-step-1, pre step-1 and post-step-2
Neurocognitive assessment	Montreal Cognitive assessment (MoCA)	Baseline and weekly during the trial period
Neurocognitive assessment	Brief Assessment of Cognition in Schizophrenia (BACS)	Baseline, post-step-1, pre-step-2 and post-step-2
Auditory hallucinations	Auditory hallucinations rating scale (AHRS), Mental Health Research Institute Unusual Perceptions Schedule (MUPS)	Baseline and weekly during the trial period
Positive symptoms	Scale for the Assessment of Positive Symptom Scale (SAPS)	Baseline and weekly during the trial period
Negative symptoms	Scale for the Assessment of Negative Symptoms (SANS)	Baseline and weekly during the trial period
General psychopathology	Brief psychiatric rating scale (BPRS)	Screening/Baseline and weekly during the trial period
tDCS and TMS side effects	TMS-related adverse effects questionnaire and tDCS related adverse effect questionnaire	After each session of tDCS and iTBS
Disability and functioning	Groningen Social Disability Schedule (GSDS)	Baseline, post-step-1, pre-step-2 and post-step-2
Functional ability	Social and occupational functioning scale (SOFAS)	Baseline, post-step-1, pre-step-2 and post-step-2
Global clinical severity	Clinician Global Impression-severity (CGI-S)	Baseline, post-step-1, pre-step-2 and post-step-2
Neurobiological tests	MRI/MRS/EEG/Perturbation tests/HRV	Baseline, post-step-1, pre-step-2 and post-step-2
Genotyping	Blood sampling	Baseline

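### Clinical outcomes are led by last observation carried forward with intention-to-treat second, which leaves the primary clinical analysis population undefined and can misclassify early drop-outs on the 30% AHRS threshold

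*Protocol article*

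**What the plan says.** The Data analysis plan fixes the lead method for clinical outcomes: "Evaluation of clinical outcomes will be based on Last-observation carried forward analysis with secondary intent-to-treat analysis". The article names no other missing-data method and no sensitivity analysis.

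The surrounding text bears on this as follows.

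- **Ratings.** Under Outcome, the clinical scales, including AHRS, "will be applied at baseline and every week till the end of the intervention". Table 1 gives the same timing for AHRS: "Baseline and weekly during the trial period". The Participant timeline spreads the 15 treatment days of a step over three weeks.
- **Response.** "Participants with <30% improvement in AHRS from baseline at the end of 2–4 weeks of the trial would be considered non-responders" (Participant timeline).
- **Drop-outs.** The concomitant-care paragraph counts as drop-outs "Participants with a change in antipsychotic dose of more than 25% from the dose at the initiation of the intervention", and likewise those who change antipsychotic or receive another neuromodulatory intervention. The post-trial care paragraph says participants are dropped for withdrawn consent, non-compliance or worsening.
- **Planned numbers.** "Anticipating ~15% dropout, we will have ~180 participants who will complete the part-1 treatment", and then "Assuming a third of the participants respond to either treatment arm, a sample of 60 and 120 will be categorised as responders and non-responders" (Sample size).
- **Status of the outcomes.** The primary outcome is change in resting-state connectivity; AHRS and the other clinical scales are secondary.

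**The concern.** LOCF is a rule for filling in missing values. Intention-to-treat is a principle about who is analysed and in which arm. Ranking one above the other does not say who is in the lead clinical analysis. That matters because every drop-out category in the article is a post-randomisation event that treatment could influence.

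LOCF also suits this endpoint badly. If improvement builds up over three weeks, a score from week 1 or 2 reflects part of a course but is judged against a threshold meant for the whole course. Carried values are then counted as if they had been observed.

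At stake are the AHRS response rates, the comparison of cTBS with c-tDCS on clinical response, and the stated precision of that comparison. Were the same labels used to form the responder groups for the connectivity analysis, some of that grouping would be wrong too.

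**Working it through.** **1. The plan's own figures.** 210 × (1 − 0.15) = 178.5, which agrees with about 180 completers. Then 180/3 = 60 responders and 180 × 2/3 = 120 non-responders. These groups contain completers only.

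**2. Drop-outs at risk of misclassification.** 210 − 180 = 30. If drop-outs would have responded at the planned one third (an assumption), 10 are would-be responders, and the full randomised set has 60 + 10 = 70 (33.3%).

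**3. Range by share reset below the threshold.** Responders under LOCF = 70 − 10 × share.

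| Share reset | Responders | Rate of 210 |
|---|---|---|
| 0% | 70 | 33.3% |
| 25% | 67.5 | 32.1% |
| 50% | 65 | 31.0% |
| 75% | 62.5 | 29.8% |
| 100% | 60 | 28.6% |

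**4. Which shares are plausible.** The documents give no trajectory, SD or drop-out timing, so all of the following is assumed. Final percentage improvement is normal with P(≥30%) = 1/3; for SD 30 the mean is 30 − 30 × 0.431 = 17.1. Rating noise has SD 10. The table gives the share of true responders below 30% when the score is carried forward.

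| Trajectory | From week 1, SD 30 (range for SD 20-40) | From week 2, SD 30 (range for SD 20-40) |
|---|---|---|
| Linear (1/3, 2/3 of final change) | 88% (82-93%) | 44% (36-55%) |
| Front-loaded (60%, 85%) | 53% (44-65%) | 24% (19-32%) |

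Of the 10 would-be responders this relabels about 4 to 9 under linear improvement (10 × 0.36 to 10 × 0.93) and about 2 to 6.5 under front-loaded improvement. Of the 20 drop-outs who would not have responded, at most about 1.5 move the other way.

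**5. Mixed timing and reason for leaving.** Simulation with 105 per arm, 15% drop-out, SD 30, rating noise SD 8, and last visit equally likely to be baseline, week 1 or week 2:

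| Drop-out | Trajectory | LOCF rate (true about 33.3%) | Responder to non-responder | Reverse |
|---|---|---|---|---|
| Unrelated to outcome | Linear | 29.5% | 8.2 | 0.1 |
| Unrelated to outcome | Front-loaded | 30.6% | 6.1 | 0.3 |
| Mainly poor improvers | Linear | 32.9% | 1.4 | 0.1 |
| Mainly poor improvers | Front-loaded | 32.9% | 1.1 | 0.2 |

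**6. Between arms, no true difference, linear, drop-out unrelated to outcome.** With 15% in each arm, LOCF creates no bias. With 20% against 10% it creates a false difference of −2.5 points, and with 25% against 5%, −5.1 points. Both splits are assumed.

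**7. Precision.** SE of the difference = √(2p(1 − p)/n per arm).

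- Information in 180 completers: √(2 × 1/3 × 2/3 / 90) = 0.070.
- 210 treated as observed, p = 1/3: √(2 × 1/3 × 2/3 / 105) = 0.065, which is 7% smaller.
- 210 treated as observed, every would-be-responding drop-out reset (p about 0.283-0.286): 0.062, which is 11-12% smaller.

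**The case against.** Several points on the other side stand.

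- **Secondary outcomes.** The LOCF sentence concerns clinical outcomes, which are secondary, and sits with the exploratory association phase. The primary outcome is connectivity.
- **The marker groups.** A reader might infer that LOCF puts would-be responders into the non-responder group used to find the marker. No passage says so. The Sample size section forms its 60 and 120 from completers, and step 2 depends on AHRS assessed 2-4 weeks on, so the article gives no route by which an early drop-out's carried score would decide entry to step 2.
- **Direction.** A reader might also infer that LOCF necessarily turns responders into non-responders. It does not. Those removed for worsening are unlikely to include many would-be responders, and for them a carried score may be better than the true endpoint.
- **Population.** It would go too far to say that the lead analysis excludes randomised patients. LOCF does not define a population and could be applied to all 210. The text supports only that the population is undefined.
- **Arm bias.** The article gives no drop-out by arm. Both arms receive real TMS pulses, and there is a provision for TBS intolerance other than dropping out.
- **SAP detail.** Model covariates and imputation settings can be left to an SAP.

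These points limit the size and reach. They do not remove the defect: the article commits itself to LOCF as lead method, so this is a stated choice rather than detail left for later, and nothing else in it repairs the choice.

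**Conclusion.** The point holds as a weakness in the stated analysis of secondary clinical outcomes. Naming LOCF as the lead method with intention-to-treat second leaves the primary clinical population undefined and handles a weekly, thresholded outcome poorly.

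The misclassification is modest and conditional: roughly 1 to 9 of about 70 would-be responders, or 0 to 5 points on the response rate. The upper end requires drop-outs to respond at the completers' rate, leave early and improve roughly linearly. The lower end applies if they are mainly poor improvers. None of these conditions is given in the documents.

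The understatement of the standard error is 7% from counting 210 as observed and reaches 11-12% only when every would-be-responding drop-out is reset. It is an understatement of uncertainty about response at the end of treatment; as a standard error for the LOCF-defined rate itself, the nominal value is close (0.0626 against a simulated spread of 0.0639 in the linear case).

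With no true difference, a false arm difference arises only if drop-out or its timing differs between arms.

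The marker analysis is affected only if LOCF labels are used there. In that case about 4-7% of the non-responder group would be wrong when drop-out is unrelated to outcome (6.1/146 to 10/150). The Sample size section classifies completers only, whereas LOCF would classify drop-outs as well, so the two sections need to be reconciled.

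**What to change.** 1. Make the primary clinical analysis all randomised participants in their allocated arm.
2. Use a likelihood-based repeated-measures model of the weekly AHRS, with arm, week, arm by week, baseline AHRS and centre (the randomisation stratum).
3. Derive responder status for incomplete cases by multiple imputation consistent with that model.
4. State how participants counted as drop-outs under the concomitant-care and post-trial care paragraphs enter the analysis, and whether AHRS recorded after such an event is used.
5. Add a sensitivity analysis for departures from missing-at-random, which is doubtful when people are removed for worsening. Keep LOCF at most as a further sensitivity analysis.
6. State which participants and which labels form the responder groups in the connectivity analysis, so that the Sample size section and the Data analysis plan agree.

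The cost is a change of wording, a little more analysis work and slightly wider confidence intervals. The weekly AHRS ratings are already scheduled, so no new visits are needed for the model.

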### Aims and hypothesis

**
*Primary*
**

To identify resting brain functional connectivity markers of response to continuous Theta Burst Stimulation (cTBS) and cathodal transcranial Direct Current Stimulation (c-tDCS) in patients with schizophrenia with persistent auditory hallucinations to improve the efficacy of interventions.Hypothesis: A differential pre-treatment resting brain functional connectivity signal will identify responders to cTBS or c-tDCS

**
*Secondary*
**

To compare the neurobiological profile of patients with schizophrenia with persistent auditory hallucinations with matched healthy controls using multi-modal data [brain imaging, Electroencephalography (EEG), TMS-tDCS perturbation study metrics, Heart Rate Variability (HRV), and neuroplastic gene polymorphisms].To examine the differential effect of cTBS versus c-tDCS on the neurobiological profile of patients with schizophrenia with persistent auditory hallucinations using multi-modal data (brain imaging, EEG, TMS-tDCS perturbation study metrics, HRV) and potential interactions with neuroplasticity gene polymorphisms.To evaluate the predictive utility of multi-modal data (brain imaging, EEG, TMS-tDCS perturbation study metrics, HRV, and neuroplastic gene polymorphisms) in identifying clinical response to cTBS or c-tDCS in patients with schizophrenia with persistent auditory hallucinations.

This study protocol adheres to the SPIRIT guidelines (
[name] *et al.*, 2023) and the example consent form and study proforma can be found as
*Extended data* (
[name] *et al.*, 2023).

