Multi-modal neurophysiological data (magnetic resonance imaging, EEG, cortical perturbation using transcranial magnetic stimulation- transcranial direct current stimulation, heart rate variability) would be acquired before and after interventions to identify predictive factors and understand the mechanistic basis of the treatment outcomes.

MRI data will be acquired in a 3T scanner (Ingenia CX, Philips). Structural MRI: T1-weighted single-shot 3D turbo field echo image.TR=2500-ms; TE=2.9-msec; FOV=256-mm; slice-thickness=1-mm; Matrix=256*256; Voxel size= 1*1*1-mm. Resting-state fMRI (RS-fMRI): Participants will be instructed to relax, not think anything actively, and lay still with their eyes open. The scan will be acquired with the following parameters: TR=2200 ms; TE=28-ms; slice-thickness=3mm; slice-number=44; Gap=0.3mm; Matrix=64*64*64; voxel=3.0-mm isotropic with 275-dynamic scans that lasts for 10 minutes and 20 seconds.

Clinical and neurobiological evaluations would be repeated before and after each intervention step (Detailed in
Table 1 and
Figure 3). Also, neuroplasticity gene polymorphisms (Brain-derived neurotrophic factor (BDNF) and catechol-O-methyltransferase (COMT) genes) will be assessed alongside clinical and neurophysiological data to identify the predictors of clinical response. At least 300 subjects matched (as a group) for age, sex, education, handedness, and socio-economic status would be chosen for the comparative analyses of neurobiological studies. They would undergo a one-time baseline assessment of clinical and neurobiological parameters. The details of the neurobiological data acquisition protocol will be described in a separate paper.

**Table 1. T1:** Scheduled Clinical assessments in the study.

Clinical Measure	Clinical Measurement tool	Timeline
Diagnosis	Structured clinical interview for DSM-5 disorders, clinician version (SCID-CV)	Screening
Handedness	Edinburgh handedness scale	Screening
Capacity to consent to participate in the research	University of California, San Diego Brief Assessment of Capacity to Consent (UBACC)	Screening and Pre-step-2
Safety screening for Transcranial magnetic stimulation (TMS)	TMS Adult safety screen (TASS)	Screening
Safety for magnetic resonance imaging (MRI)	MRI-safety checklist	Screening
Clinical details	Comprehensive semi-structured proforma	Screening/Baseline
Global response to each of past antipsychotic trials	Clinical global impression-improvement	Screening/Baseline

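### The primary prediction model uses resting-state fMRI alone, with no clinical-only benchmark, so it cannot show whether connectivity adds to the baseline clinical data the trial already holds

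*Protocol article*

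**What the plan says.** The primary hypothesis (protocol article, Aims and hypothesis) is: "A differential pre-treatment resting brain functional connectivity signal will identify responders to cTBS or c-tDCS". The Data analysis plan divides the work into association and prediction.

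- **Association phase.** This is exploratory. It looks at biographic features and at "disorder-specific (age-at-onset, medication, the severity of symptom, etc.) features that influence TMS-derived neuroplasticity metrics, MRI, EEG, HRV, and gene polymorphism measures".
- **Prediction phase.** Combination features are sought "from resting-state fMRI as the primary objective; combining across data modalities will be the secondary objective". The models are to be validated with an independent dataset. Bayesian-network or mediation models are to be explored last.

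The matching secondary aim lists what is to be combined: "To evaluate the predictive utility of multi-modal data (brain imaging, EEG, TMS-tDCS perturbation study metrics, HRV, and neuroplastic gene polymorphisms". Clinical variables are not on that list.

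Clinical data do appear elsewhere. Under Trial procedures and evaluations, the gene polymorphisms "will be assessed alongside clinical and neurophysiological data to identify the predictors of clinical response". Under Data management, "Different streams of data (ex. Clinical, MRI, EEG etc.,) would be linked using codes". Table 1 schedules AHRS, SAPS and SANS at baseline.

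**The concern.** Responders and non-responders are not randomised groups, so they can differ at baseline in severity, medication, age or illness duration. The plan itself treats several of these as influences on MRI measures. Severity is also close to the outcome: response is a percentage improvement in AHRS from baseline (Participant timeline, Step-2), so baseline AHRS is its denominator.

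If such a variable predicts response and also shifts connectivity, an fMRI-only model will show some predictive performance even when connectivity has no information of its own. Validation in an independent dataset does not remove this, because a proxy for severity replicates as well as a true marker does.

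At stake is the clinical reading of the result. The Introduction and Discussion present the trial as a guide to treatment choice. A scan is worth acquiring for that purpose only if it tells the clinician more than the rating scales and drug history already on file. The prediction phase as described contains no comparison that could show this.

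**Working it through.** **1. The plan's own figures (Sample size).** 210 × 0.85 = 178.5, stated as about 180. Then 180/3 = 60 responders and 180 − 60 = 120 non-responders. At 1:1 allocation this is 60/2 = 30 responders and 120/2 = 60 non-responders per arm. The chain reproduces, and no stated number is wrong.

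**2. What each stated analysis can show.**

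| Stated analysis | Can it show that connectivity adds to clinical data? |
|---|---|
| Association phase: clinical features against MRI measures | It may reveal a proxy, but it is exploratory and sets no condition on the primary model |
| Primary prediction: fMRI features only | No |
| Secondary prediction: modalities combined | No. The aim's list has no clinical variables, and no comparison with clinical data is stated |
| Independent validation | No. It tests replication |
| Bayesian-network or mediation models | Possibly, but exploratory and with no criterion |

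**3. Size of the mechanism (illustration).** The following are assumed and are not in the documents: a clinical variable with AUC 0.65 to 0.75 for response; a within-group correlation r of 0.3 to 0.5 with one connectivity feature; no effect of that feature on its own; normal distributions with equal variance.

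- Clinical difference in SD units: D = √2 × z(AUC). AUC 0.65, 0.70 and 0.75 give D = 0.545, 0.742 and 0.954.
- Connectivity difference: d = r × D, from 0.3 × 0.545 = 0.163 to 0.5 × 0.954 = 0.477.
- AUC of connectivity alone: Φ(d/√2), from 0.546 to 0.632.
- Non-centrality of a two-sample t-test: d × √(n₁n₀/(n₁+n₀)). At 60 vs 120 the root is √40 = 6.325, giving 1.03 to 3.02.

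Probability of two-sided P<0.05 (non-central t):

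| Clinical AUC | r | 60 vs 120 (both arms) | 30 vs 60 (one arm) |
|---|---|---|---|
| 0.65 | 0.3 | 0.18 | 0.11 |
| 0.70 | 0.4 | 0.46 | 0.26 |
| 0.75 | 0.5 | 0.85 | 0.56 |

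**4. Check that a clinical term removes it.** A simulation (2,000 runs per setting) used a severity difference of 0.5 to 0.8 SD, correlations of 0.3 to 0.7, and again no own effect of connectivity. Connectivity alone was significant in 17% to 94% of runs at 60 vs 120, and in 10% to 71% at 30 vs 60. With severity in the model the rate was 4% to 6%, which is the nominal level.

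**The case against.** **Comparator models belong in the SAP.** Benchmarks and performance measures are often set there, and only a condensed article is at hand. This limits the point: if the full protocol or SAP already sets a clinical benchmark, the point is met. But the article does state the primary feature set and the order of the models, and the point is about that stated method. Making fMRI primary is consistent with the primary aim and is not an error in itself.

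**The plan does not ignore clinical data.** A reader might infer that connectivity is never set against clinical variables. The documents do not support that. The association phase examines severity and medication against MRI measures, the genetic work is read alongside clinical data, clinical data are a linked stream, and the causal models could probe a path from severity through connectivity to response. What is missing is narrower: a benchmark or added-value comparison in the prediction phase, and a link from the association phase to the primary model.

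**A proxy need not go unnoticed.** For the same reason, one cannot say that a severity proxy would be reported as a marker, only that it could be.

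**A prognostic proxy does not misdirect the choice of treatment.** A reader might infer that the trial would recommend the wrong one of cTBS and c-tDCS. That does not follow. A variable that predicts response equally under both treatments gives no basis for choosing between them. The hypothesis concerns a differential signal, and for a proxy to mimic that, severity or medication would have to predict response differently by treatment. Nothing here assumes or calculates this. The illustration bears on the general response signals that the Sample size section also seeks.

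**The probabilities are not the planned model's error rate.** They describe one uncorrected test of one feature. The plan speaks of corrected signals and multi-feature validated models. This stands, and the figures show only that the mechanism is not negligible.

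**Conclusion.** The point holds in a limited form. As stated, the prediction phase cannot show whether resting-state connectivity improves on baseline clinical data, and none of the planned safeguards is tied to that question. A feature that partly mirrors severity or medication could be put forward as a response marker without evidence of added value.

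The size is uncertain. The 0.18 to 0.85 range rests wholly on the assumed clinical AUC and correlation, for which the documents give no values. The plan's stated numbers are sound and the sample size is unaffected. Connectivity may still prove to be a marker in its own right; the stated models would simply not show whether it is. The change is worth making because the trial's purpose is to inform treatment choice and the comparison needs no new data.

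**What to change.** Add to the prediction phase a baseline-clinical model using AHRS, SAPS/SANS, age, sex, age at onset, antipsychotic dose and centre, fitted in the same training and validation splits as the fMRI model. Beside fMRI-only performance, report the out-of-sample gain of clinical-plus-fMRI over clinical-only (AUC or Brier score, with 95% CI), overall and by treatment.

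The fMRI-only model can stay the primary objective, since the stated aim is to identify connectivity markers. Any claim that connectivity is useful for choosing treatment should rest on the gain. State also how the association-phase findings on severity and medication bear on the reading of the primary model.

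The cost is a little more analysis of data already planned, with no added visits, scans or patients. The downsides are that connectivity may look less valuable than its stand-alone performance suggests, and that the by-treatment gain, with about 30 responders per arm, will be imprecise.
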